## **Evaluation of AEs**

### **Definition of SAEs**

SAE are defined as any AE that meet one or more of the following criteria:

1. Results in death
2. Is life-threatening
3. Requires inpatient hospitalization or prolongation of existing hospitalization
4. Results in persistent or significant disability or incapacity
5. Is a medically important event that may jeopardize the subject
6. Other events that are equivalent in seriousness to those listed above
7. Congenital anomaly or birth defect in offspring

The following types of hospitalization are not considered SAEts under item 3, "hospitalization":

- Hospitalization solely for the purpose of conducting treatments or examinations that are scheduled prior to obtaining informed consent (e.g., scheduled surgeries or tests)
- Hospitalization for administrative or social reasons (e.g., receiving intravenous treatment, or cases where the subject's residence is far from the medical facility, making same-day treatment difficult)
- Hospitalization not intended for the treatment of an adverse event (e.g., hospitalization for examinations or health checkups)

### **Severity of AEs**

The severity of AEs in this study is classified as follows:

| Severity | definition |
| --- | --- |
| Mild | Symptoms or signs are recognized but do not interfere with daily activities, or are transient and recover without treatment, leaving no sequelae. |
| Moderate | Interferes with daily activities or requires medical intervention. |
| Severe | Significantly interferes with daily activities and requires surgical or other intensive intervention; may result in death or permanent dysfunction affecting daily life. |

### **Causal Relationship with the Study Product**

The principal investigator (or sub-investigator) must assess the causal relationship between the adverse event (AE) and the study product. The relationship should be classified as either **“Not ruled out”** or **“Ruled out.”** If the investigator cannot reasonably deny a causal relationship with the study product, the AE is assessed as **“Not ruled out.”**

## **Reporting of AEs**

### **Reporting Period for AEs**

AEs must be reported from the initiation of study product administration until 30 days thereafter or until the final study visit specified in the protocol, whichever is later. Any SAE for which a causal relationship with the study product cannot be ruled out must be reported **regardless of the reporting period**, as long as it occurs before the end of the study period.

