**Observation Period**: **30days**

The primary outcome will be the measurement of the total drainage volume within 12 hours of ICU admission. As a secondary outcome, patients will be followed for 30 days after the administration of the investigational treatment.

Abbreviations

| AE | Adverse event |
| --- | --- |
| ACT | Activated clotting time |
| ALT | Alanine aminotransferase |
| APTT | Activated partial thromboplastin time |
| AST | Aspartate aminotransferase |
| ATIII | Anti thrombin III |
| BNP | Brain natriuretic peptide |
| CABG | Coronary artery bypass grafting |
| CDC | Centers for disease control and prevention |
| CK | Creatine kinase |
| CPB | Cardiopulmonary bypas |
| CRF | Case report forms |
| CRP | C-reactive protein |
| FAS | Full analysis set |
| FBS | Fast blood sugar |
| FDP | Fibrin/fibrinogen degradation products |
| FFP | Fresh frozen plasma |
| ICU | Intensive care unit |
| ITT | Intent-to-treat population |
| LDH | Lactate dehydrogenase |
| PPS | Per protocol set |
| PT-INR | Prothrombin time-international normalized ratio |
| RBC | Red blood cell |
| SAE | Serious adverse event |
| SSI | Surgical site infection |

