## **Administration of the Study Treatment**

Consent and provisional registration are completed before the day of surgery. The final registration and randomization occurs during CPB. From the point of CPB weaning (protamine administration), the study product is administered based on the hemoglobin levels.

< Administration criteria for the study treatment>

If hemoglobin is less than 10.0 g/dL or is anticipated to drop below this level, transfusion is administered per group assignment.

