### **Salvaged RBC Group (Investigational Product Group)**

From weaning off CPB until exiting the operating room, salvaged RBC is administered preferentially over allogeneic RBC to treat anemia. Residual blood in the CPB circuit (post-CPB blood) is collected immediately after the removal of the arterial and venous cannulas using the cell salvage device. If anemia is not corrected after administering all available salvaged RBC or if correction is not expected, allogeneic RBC is transfused.

If salvaged RBC become available during the transfusion of allogeneic RBC, the transfusion of allogeneic RBC is suspended and replaced with salvaged RBC. If salvaged RBC is unavailable when needed, allogeneic RBC is used.

After recovering the post-CPB blood, a 2 mL sample of the first returned salvaged RBC is collected and sent to an external laboratory to measure the heparin concentration.

After ICU admission, allogeneic RBC is used for the treatment of anemia.

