## **Visit 4. End of Study**

Observations and examinations are performed 30 days after the initiation of study treatment (acceptable range: ±5 days). Data is collected from the critical care information system (AXIS) and electronic medical record system (MegaOak).

| 1) Study Treatment Information | |
| --- | --- |
| Treatment Information | - Postoperative chest tube blood loss within 12 hours after ICU admission - Total chest tube blood loss until removal - Transfusion volume within 24 hours after ICU admission (RBC, FFP, cryoprecipitate, platelet concentrates) - Duration of mechanical ventilation - Length of ICU stay - Postoperative hospital stay - Date of discharge |
| Discontinuation/interruption of treatment | Presence or absence; if applicable, record the date, reason, and subsequent management |
| 2) Clinical and Laboratory Data | |
| Laboratory tests  (obtained on the day after surgery) | White blood cell count, hemoglobin, platelet count, total protein, albumin, total bilirubin, direct bilirubin, AST, ALT, creatinine, LDH, CK, CK-MB, sodium, potassium, chloride, calcium, CRP, PT-INR, APTT, fibrinogen |
| 3) Adverse Event Reports | |
| AEs | Date of onset, event name, known or unknown, seriousness, severity, causal relationship, treatment, outcome, date of outcome confirmation, readmission status (presence/absence), date of readmission, date of discharge, and other relevant details |
| 4) Outcome Information | |
| Survival status | Outcome: alive, deceased, or lost to follow-up  Date of last confirmed survival or date of death; in case of death: cause of death If lost to follow-up: reason for discontinuation of follow-up |
| Stuidu withdrawal | Presence or absence; if applicable, record the date and reason for withdrawal |

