# **Evaluation and Reporting of AEs**

## **Definition of AEs**

An AE refers to any untoward medical occurrence in a subject who has received the study treatment, regardless of whether a causal relationship with the study treatment can be established. A side effect is defined as an AE for which a causal relationship with the study product cannot be reasonably excluded.

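### The adverse event definition and reporting start depend on receipt of study product, which is conditional after randomisation, so the rules omit untreated randomised patients and conflict with the protocol's own visit schedule

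*Protocol*

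**What the plan says.** Four places tie safety follow-up to receipt of product:

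- Section 9.1 defines an AE as "any untoward medical occurrence in a subject who has received the study treatment".
- Section 9.4.1: "AEs must be reported from the initiation of study product administration until 30 days thereafter", or up to the last protocol visit if that comes later.
- Section 8.4 (Visit 4): "Observations and examinations are performed 30 days after the initiation of study treatment", with a tolerance of 5 days either way.
- The observation period note after the study overview: "patients will be followed for 30 days after the administration of the investigational treatment".

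Receipt is not guaranteed. Section 7.5 places final registration and randomisation during CPB and then sets a condition: "If hemoglobin is less than 10.0 g/dL or is anticipated to drop below this level, transfusion is administered per group assignment". In the salvage arm, section 7.5.1 adds: "If salvaged RBC is unavailable when needed, allogeneic RBC is used".

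Other places need no product. Section 8.3 (Visit 3) collects AEs after CPB weaning on the day of surgery. The schedule table puts Visits 2 and 3 on day 0 and Visit 4 on day 30, and its legend has a symbol for items assessed throughout the study. Section 9.2 asks for every AE during the study period to be recorded.

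**The concern.** A randomised trial needs one safety definition and one clock that apply to every randomised patient. Here both start with an event that comes after randomisation and may not happen. Three things follow from the wording of sections 9.1 and 9.4.1:

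1. A randomised patient who receives no product has no AE by definition and no date on which reporting starts.
2. For treated patients, an event between CPB weaning and the first unit is outside the reporting window, although Visit 3 collects it.
3. In the salvage arm it is unclear whether allogeneic red cells given first, because salvaged cells are not ready, start the clock. Section 5 names salvaged cells the investigational product and allogeneic cells the control product, and section 9.4.1 says only study product. In the control arm the same unit at the same moment clearly starts it.

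What is at stake is complete and even-handed AE and serious AE capture, and with it the infection outcome.

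**Working it through.** The protocol gives no figure for the share of randomised patients who receive no product, so there is none to reproduce. The check is mainly a comparison of provisions.

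**Step 1. Can a randomised patient go untreated?** Yes. Section 7.5 makes product conditional on hemoglobin. Section 7.5.3 also lets study treatment stop for reasons that could arise before the first unit: mechanical circulatory support, a change to a very high-risk procedure or, in the salvage arm only, contaminated salvaged blood. Non-receipt therefore need not be random or equal between arms.

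**Step 2. Which rules reach that patient?**

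| Provision | Depends on product? |
|---|---|
| 9.1 AE definition | Yes |
| 9.4.1 AE reporting start | Yes |
| 8.4 and overview note, 30-day follow-up | Yes, by wording |
| 8.3 Visit 3 AE collection | No, from CPB weaning |
| Schedule table, day 0 and day 30 | No |
| 9.2 recording during the study period | No, but uses the 9.1 definition |
| 9.4.2 serious AE reporting | No, but uses the 9.3.1 definition, which rests on 9.1 |

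Section 9.3.1 defines a serious AE as an AE that meets a seriousness criterion. So a death in an untreated patient is, read literally, neither an AE nor a serious AE. The two extensions in section 9.4.1 do not help. Taking the later end date moves only the end of the window, and the clause that lifts the time limit covers only serious AEs possibly caused by the product.

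**Step 3. Which safety outcomes rest on the AE record?** Section 4.3 lists three. Kidney injury is timed from surgery and hematuria is assessed on ICU admission, so neither depends on product. For infection, Visits 3 and 4 list no data item other than the AE record, so this outcome inherits the section 9.1 restriction.

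**Step 4. How many patients?** Under an assumed untreated share f, the expected number is 142 × f and the chance of at least one is 1 − (1 − f)^142.

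- f = 1%: 142 × 0.01 = 1.4 patients; 1 − 0.99^142 = 0.76.
- f = 5%: 142 × 0.05 = 7.1 patients; chance above 0.99.
- f = 10%: 142 × 0.10 = 14.2 patients; chance above 0.99.

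**Step 5. How far can the clock differ by arm?** All study product is given between CPB weaning and leaving the operating room. For an assumed lag of 1 to 6 hours, 1/(24 × 30) = 0.1% and 6/(24 × 30) = 0.8% of the 30 days. Six hours is 6/(24 × 5) = 5% of the 5-day Visit 4 tolerance.

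**The case against.** The strongest reply is that the protocol already supplies the right anchor. Visit 2 data run up to CPB weaning, and its column in the schedule is labelled as preceding the start of study treatment. Visit 3, the treatment visit, begins at weaning. The start of treatment can thus be read as CPB weaning, which dates Visit 4 for everyone. The AE row of the schedule appears empty, but the legend's symbol for continuous assessment suggests an arrow lost in text extraction. Visit 4 data come from clinical records, and section 7.7.1 continues data collection after treatment is discontinued. In practice, staff would probably record events in untreated patients.

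Most of this stands, and it rules out some stronger readings. A reader might infer that untreated patients have no final visit or lose their 12-hour drainage data. The documents do not support this: the schedule dates the visit, and drainage is timed from ICU admission or end of surgery. A reader might also infer that the whole safety comparison is confined to patients selected after randomisation. That does not follow, since kidney injury and hematuria have their own anchors and the analysis populations are left to the statistical analysis plan. Nor is the difference in clock by arm material to the 30-day window. It is a matter of hours within one operation, AEs are recorded by date of onset, and only intraoperative events could be affected.

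The reply does not remove the wording of sections 9.1 and 9.4.1. These are the operative definition and reporting rule. They speak of receipt and administration, and they are narrower than the visit schedule.

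**Conclusion.** The point holds as a conflict between stated rules. Sections 9.1 and 9.4.1 leave out randomised patients who receive no product and, for treated patients, the interval from CPB weaning to the first unit. Section 8.3, the schedule and section 9.2 point the other way. The consequences are confined to general AE and serious AE reporting and to the infection outcome. Severity is minor to moderate.

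The number of patients affected is unknown, and the 1% to 10% range above is an assumption. The true share may be low: every randomised patient is at high bleeding risk and has already received allogeneic red cells during CPB, and an anticipated fall in hemoglobin is enough to trigger product. Even at 1%, at least one such patient among 142 is more likely than not. The conclusion also assumes that no other trial document overrides sections 9.1 and 9.4.1.

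**What to change.** In sections 9.1 and 9.4.1, define AEs in every randomised patient, whether or not product is given, and start reporting at CPB weaning on the day of surgery. Visit 3 already uses this anchor. For consistency, count the 30 days in section 8.4 and in the overview's observation period note from the same point, with the day of surgery as day 0 as in the schedule. With this anchor, it no longer matters for timing whether allogeneic cells given first in the salvage arm count as study product. One added clause should say what applies if weaning is never achieved, so that the new anchor has no gap of its own.

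The cost is wording in four places. Treatment, sample size and visits do not change, and the data are already collected in routine care. This is a free improvement.

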### **Reporting Procedure for SAEs**

All personnel involved in the conduct of this study must follow the procedures below upon learning of an SAE in a study participant.

< Procedure >

1. The SAE is promptly reported to the principal investigator.
2. The principal investigator must report the SAE to the institutional ethics committee and study supervisor without delay.
3. The principal investigator also report the SAE to the head of the institution and take appropriate measures based on the protocol and institutional standard standard operating procedures. The relevant study personnel are informed of the events.
4. Upon receiving a response from the ethics committee, the principal investigator must report it to the institutional head and, if the committee provides specific recommendations, include the details of the corresponding actions in the report.
5. If the SAE is both unexpected and causally related to the study product, the principal investigator must report the incident and subsequent actions to the Ministry of Health, Labour, and Welfare of Japan using the designated format (Ethical Guidelines Form 3) and disclose the information on the institutional website.

## **Anticipated AEs**

The anticipated AEs associated with the administration of the study product are listed below.

### **Common AEs**

- Fever
- Hypothermia
- Hyperkalemia
- Dilutive coagulopathy
- Acidosis

### **Specific to Allogeneic RBC Transfusion**

- Hemolytic reactions
- Transfusion-associated dyspnea
- Allergic reactions
- Transfusion-related acute lung injury
- Transfusion-associated circulatory overload
- Post-transfusion purpura
- Graft-versus-host disease
- Transfusion-transmitted infections (viral, bacterial, protozoal, or other)
- Iron overload
- Hypocalcemia

### **Specific to Salvaged RBC Transfusion**

- Bacterial infections
- Hemolytic reactions

Other surgery-related complications not listed above may also occur and are recorded as adverse events.

# **Study Period**

Planned Study Period: From the date of ethical approval to March 31, 2030

Enrollment Period: From the date of ethical approval to September 30, 2026

Observation Period: From the date of ethical approval to November 4, 2026

# **Target Sample Size**

The target number of participants for final registration is 142 (71 in the salvaged RBC group and 71 in the allogeneic RBC group).

# **Statistics Considerations**

Statistical analysis is conducted in accordance with a separate document, the Statistical Analysis Plan.

# **Ethical Considerations**

## **Applicable Guidelines and Regulations**

This study is conducted in compliance with the ethical principles of the Declaration of Helsinki, Ethical Guidelines for Life Science and Medical Research Involving Human Subjects, and study protocol.

## **Procedures** **for Study Implementation**

Before initiating the study, the principal investigator must obtain approval from the institutional ethics committee and authorization from the head of the research institution.

## **Reporting to the Head of the Institution and Ethics Committee**

1) Reporting during the study

Researchers must report the following events to the principal investigator. In cases that fall under items 2 or 3, researchers must promptly report to the head of the research institution and, as needed, suspend, discontinue, or amend the study protocol (in accordance with Article 11, Sections 1, 2(2), and 2(3) of the Ethical Guidelines).

(1) Events or information that compromise or may compromise the ethical or scientific validity of the study

(2) Events or information that compromise or may compromise the integrity of the study implementation or the reliability of the study results

(3) Serious concerns related to human rights or the conduct of the study, such as the leakage of information related to the study

2) Periodic reporting

The principal investigator must submit an annual report to the ethics committee and the head of the institution regarding the progress of the study and the occurrence of adverse events.

3) Reporting at study completion (including premature termination)

The principal investigator must report the completion of the study to the ethics committee and the head of the institution in a timely manner.

## **Overall Assessment of Benefits and Burdens to Study Participants**

### **Benefits to participants and potential benefits of the study**

If this study demonstrates that the use of salvaged RBC during cardiovascular surgery does not increase postoperative bleeding, it may support the effective use of salvaged RBC that would otherwise be discarded and reduce the volume of allogeneic RBC transfusions. However, it is unlikely that the participants receives direct medical benefits during the study period.

### **Burden on study participants**

This study included blood sampling to measure heparin concentration in salvaged RBC for research purposes. However, only 2 mL of blood is collected from the processed salvaged RBC, which involves no risk of puncture and poses an extremely low risk of exacerbating anemia.

### **Anticipated risks to study participants**

There is a possibility of adverse events related to the study product, as described in Section 9.5. The risk of anemia due to blood sampling for research purposes is considered extremely low. Personal information is processed to prevent the immediate identification of individuals; thus, the risk of harm due to data leakage is considered to be low.

### **Measures to minimize risk**

Since personal information is processed, the risk of harm due to external data leakage is considered to be low.

### **Overall Evaluation**

The overall benefits of this study are considered to justify the potential risks and burdens of the participants.

### **Compensation for participation**

No compensation is provided to the participants for their involvement in this study.

## **Handling of inquiries from participants and their representatives**

The study information sheet includes the contact information (address, telephone number, etc.) of the study office as a point of contact for inquiries, and the office いis available to respond to questions or concerns from the participants and their representatives.

## **Preparation and Revision of the Study Information Sheet and Consent Form**

### **Preparation of documents and approval by the institution**

The principal investigator is responsible for preparing the study information sheets and consent forms. These documents must be submitted to the head of the institution and approved before the study initiation.

### **Required content of the study information sheet**

The study information sheet must include the following items, as specified in the Ethical Guidelines for Life Science and Medical Research Involving Human Subjects:

1. Title of the study and a statement that the head of the institution has approved its implementation
2. Names of cooperating institutions, names and affiliations of contributors providing existing specimens or data only, and names and affiliations of all principal investigators
3. Purpose and significance of the study
4. Methods and duration of the study, including the intended use of collected specimens and data
5. Reason for participant selection
6. Burden on participants, anticipated risks, and expected benefits
7. That participants may withdraw their consent at any time, and if there are limitations to such withdrawal, the reasons must be stated
8. That refusal or withdrawal of consent does not result in any disadvantageous treatment
9. Method of information disclosure about the study
10. That participants may request access to the study protocol and relevant information within the limits of protecting personal data and maintaining research originality, and how to make such requests
11. Handling of personal information, including details of anonymization or non-identifiable processing
12. Methods for storage and disposal of specimens and data
13. Funding sources and potential conflicts of interest of the institution or individual researchers
14. Handling of study results
15. How the study team responds to inquiries from participants or their representatives
16. Whether participants incur any financial burden or receive compensation
17. Information about alternative treatment options if the study involves procedures beyond standard care
18. Information about post-study care if the study involves procedures beyond standard care
19. Whether compensation is provided for study-related harm, and the details if applicable
20. If specimens or data may be used in unspecified future research or shared with other institutions, the means by which participants can confirm the content, the purpose, and the potential receiving institutions
21. If the study involves more than minimal invasion and includes interventions, a statement that study monitors, auditors, and the ethics committee may access relevant data and specimens for monitoring, auditing, and review purposes, provided participant confidentiality is protected

